### Randomization

Participants who are eligible for the study and complete all baseline measurements will be randomly assigned to 1 of the 3 intervention arms using a computer-generated program. Randomization will take place in groups following rounds of advertising and is stratified based on sex, age, and years since cancer diagnosis. Couples or friends who sign up for the study together will be randomized together to avoid contamination across groups. Randomization will take place following completion of all baseline assessments and a week before the 12-week exercise sessions are scheduled to begin. Participants will be notified via a mailed letter and follow-up phone calls confirming their randomized group and logistics (parking and directions) for their 12-week exercise sessions. This is an open label trial with no blinding of participants or assessors.

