### Exercise intervention and active control groups

#### Yoga arm

The yoga intervention consists of two weekly, 90-min group sessions for 12 weeks. The style of yoga selected for the intervention is Hatha yoga, the most popular form of yoga practice in the USA [28] which focuses on practicing physical poses, breathing, and meditation. STAY Fit yoga sessions will be held at a local yoga studio and taught by a certified yoga instructor, who has been instructing and practicing for more than 20 years. Each 90-min session is structured such that participants perform 60-min of stretching and poses (*asana*), 15 min of guided breathing practice (*pranayama*), and 15 min of guided meditation. Table 2 depicts a sample yoga session. Sessions are designed at a beginner level for the first few weeks, with a focus on helping participants develop good form, proper alignment, and postures for the asanas. Props used during the sessions include a yoga mat, chair, blanket, and blocks.

**Table 2 Tab2:** Sequence of Hatha yoga and stretching-toning exercises from week 1 of the STAY Fit Trial

Yoga	Stretching and toning
Poses (*asanas)*	Back arch
*Ardha Matsyendrasana*—twist in simple seated pose	Forward bend
*Marjaryasana/Bitilasana*—cat and cow	Squat
*Tadasana*—mountain pose	Military press
**Utkatasana*—chair pose	Walking dips
*Urdhva Hastasasana*—upward salute	Bicep + fly arm cycle
**Virabhadrasana*—warrior 1 and 2	Wood chop
**Purvottanasana*—intense side stretch	Tricep extension
*Viparita Karani*—Supported legs on the seat of a chair	One leg stand
*Supta Baddha Konasana*—reclining bound angle pose	Side leg abductions
*Supported Savasana*—corpse pose	Bicycle abdominal twist
Breathing (*pranayama*)	
3 parts breath in *Supta Baddha Konasana*	
Mediation	
Guided meditation/body scan while in supported *savasana*	

Note: *Using chair for support

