#### Aerobic walking intervention arm

Participants randomized to the walking intervention arm will meet three times a week, 60 min a session, for the 12-week intervention. The intensity of each walking session will be individualized for each participant. The 12-week structure of the walking sessions, including the intensity and duration for each week’s sessions, is presented in Table 3. The rating of perceived exertion (RPE) and target heart rate (HR) zones were selected in accordance with the ACSM exercise prescription guidelines for cancer survivors. Within each 4-week block, participants started at the lowest recommend intensity for 15 min, gradually increasing the duration to 40 min with the target HR zone. Prior to the start of the intervention, researchers will calculate each participant’s target HR zones using the Kavonen formula [29] ([(HR_max_ − HR_rest_) × % training intensity] + HR_rest_), where HRmax = 220 − age and HRrest = resting heart rate recorded at baseline submaximal treadmill test. All walking sessions are led by trained exercise leaders, who are trained with the detailed protocol for the sessions, and complete 2-h-long orientations to review the manual of procedures and protocols including participant safety, leading warm up and cool down exercises and adapting the intensity of exercise to target the HR zones. During each session, exercise leaders are responsible for monitoring the participant’s heart rate every 5 min to ensure they stay within their designated heart rate zone. Participants will be allowed to freely change the speed and/or incline during the session to stay in the target HR zone. If needed, participants will be given wrist and/or ankle weights to wear to keep them at a higher intensity. Sessions will begin with a 5-min warm up including dynamic stretching and brief aerobic activity (e.g., marching in place, high knees) and end with a 5-min slow walking cool down and static stretching until the participant HR returns to pre-exercise resting levels.

**Table 3 Tab3:** ACSM’s aerobic exercise prescription for cancer survivors and protocol for the STAY Fit walking group

Weeks	1–4	5–8	9–12
Rating of perceived exertion	12–13	14–15	16–17
Target heart rate zone (% of heart rate reserve)	40–59	60–70	70–89
Duration (minutes)	15–40	15–40	15–40

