#### Stretching and toning control arm

Participants randomized into the stretch and toning group will participate in sessions three times a week for 60 min each for the duration of the 12-week program. This group will participate in exercises that target all major muscle groups and work toward balance, toning, and flexibility. A sample stretching and toning exercise sequence is presented in Table 2. A given week will consist of the same exercises, but more reps and/or sets will be added over the course of the week’s sessions (Monday to Wednesday to Friday) building from 1 to 2 sets and 8 to 12 reps. Stretches and balance exercises were timed starting at 10 building up to 30 s. Exercises are designed to be progressive and challenging over the 12-week study period. At the beginning of each session, participants will walk around the perimeter of the room for 5 min and then engage in a 5-min warm up stretching routine. During the warm-up and before beginning the exercises, the leaders will inform the participants about the exercises, repetitions, and sets for the session. The exercise leaders will track the number of sets, repetitions, and time for exercises that are time-based (e.g., planks). Exercise leaders will provide posture and breathing cues throughout the session and demonstrate modifications for exercises when a participant presents mobility or functional limitations. The sessions will end with a 5-min cool down consisting of static stretching. Stretching and toning sessions will take place in an exercise studio and will be led by trained exercise leaders. Similar to the walking exercise leaders, these are given a manual detailing the protocol for the sessions and complete 2-h long orientation and training sessions to learn about participant safety, warm-up, stretching and toning exercises and modifications, and cool down stretches.

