#### Exercise logs, attendance, and adherence

Prior to each session, participants in all groups will be fitted with a chest-strap heart rate monitor (Polar Model F1), which will record their heart rates over the session. At each session, participants will be given an exercise log, where they are to record their resting heart rate, average heart rate for the session, their self-reported rating of perceived exertion using the Borg scale [30], and self-reported enjoyment (a 1–5 Likert scale). The supervising exercise leader will keep track of the total minutes of exercise for the day and will review the logs for completeness before concluding the exercise session.

Attendance will be monitored by the respective exercise leaders for the 3 groups. A binder with attendance sheets for the 12 weeks will be presented to the exercise leaders at the first exercise session. Exercise leaders will be responsible for recording attendance and noting announced and unannounced absences. To promote adherence to the study protocols, participants will receive follow-up phone calls for any unannounced absences. They will also be given a mid-session feedback report (6 weeks, i.e., halfway into the intervention), providing averages of their weekly heart rates, rating of perceived exertion, enjoyment ratings, overall attendance percentage, and personalized feedback from their respective exercise leaders. Lastly, two times throughout the study period, exercise leaders will hold a raffle with prizes donated from local businesses (free fitness classes at a local gym) that can be redeemed after the trial ends.

In the event where a participant has decided to drop out of the study, their decision will be noted, and the participant will be contacted to administer follow-up assessments. Participants must have attended at least one session in order to be contacted for follow-up.

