### Statistical analysis

Data will be analyzed using SPSS 24.0 (IBM Corp., Armonk, NY). Each of the cognitive domains assessed will be analyzed separately. From each of the assessments administered, latent variables will be created to represent a global cognitive score for each domain. These variables will be created for both baseline and post-intervention test scores. Given the pilot nature of this study, we will focus on descriptive statistics and calculating effect sizes (Cohen’s d values). Data characteristics permitting (normality, multi-collinearity, sample size), we may conduct additional secondary analyses. For example, a time (baseline, follow up) × group (yoga, aerobic, stretching-toning) repeated measures analyses of covariance controlling for relevant covariates (possible covariates include age, education, stage of cancer, months since diagnosis, attendance, and baseline performance) can be employed to explore intervention effects for each of the cognitive domains. Similar repeated measures analyses could examine intervention effects for cardiovascular fitness and the tertiary psychosocial outcomes. Given that this is a pilot study, no additional subgroup or adjusted analyses are planned. An intent-to-treat analysis approach will be used for any dropouts who completed at least one exercise session. Missing data will be handled using a mean imputation approach. Participants’ exercise session attendance and physical activity performed outside of the session (as reported in home logs) will be factored into analyses as appropriate to control for participants’ adherence to study protocols.

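### The intent-to-treat rule omits, and follow-up skips, participants who attend no session after learning their arm, so the effect sizes can be biased

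*Protocol article*

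**What the plan says.** All references are to the protocol article.

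- **Analysis set** (Statistical analysis): "An intent-to-treat analysis approach will be used for any dropouts who completed at least one exercise session". The same section handles missing data by mean imputation and makes descriptive statistics and Cohen's d the main output.
- **Follow-up** (Exercise logs, attendance, and adherence): "Participants must have attended at least one session in order to be contacted for follow-up".
- **Order of events** (Randomization): "Randomization will take place following completion of all baseline assessments and a week before the 12-week exercise sessions are scheduled to begin". Then "Participants will be notified via a mailed letter and follow-up phone calls confirming their randomized group". Also: "This is an open label trial with no blinding of participants or assessors".
- **What the arms ask of participants**: "The yoga intervention consists of two weekly, 90-min group sessions for 12 weeks", at a local yoga studio. Walkers "will meet three times a week, 60 min a session". The stretching and toning group "will participate in sessions three times a week for 60 min each", in an exercise studio.

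No other section brings a randomised participant who attended no session back into follow-up or analysis.

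**The concern.** Intent-to-treat means that everyone randomised is analysed in the arm assigned. Here the term covers only those dropouts who reached a first session. Leaving out people who never start can be harmless when nobody knows the allocation until treatment begins. In this trial participants know their arm about a week earlier, and the arms are visibly different, so the decision to start comes after the allocation and can be shaped by it. Couples and friends are randomised together, so one refusal could remove two people from the same arm.

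At stake are the effect sizes. They would be computed on a group partly selected by its reaction to allocation, and the Discussion says that the pilot should inform a larger efficacy trial. A separate analysis plan could redefine the set, but it could not supply 12-week outcomes that the follow-up rule says are not sought.

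**Working it through.** **The plan's own figure.** The article plans 75 participants, 25 per arm. The total of 75 is reproduced by the between-groups test in a two-time-point repeated-measures design with f = 0.35, alpha = 0.025 and an assumed within-person correlation of 0.5: noncentrality 0.35² × 75 × 2 / (1 + 0.5) = 12.25, power 0.806. The article does not name its formula, and a one-way analysis of variance at the same alpha would need 98. The point below uses only the 25 per arm.

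**The two rules side by side.** The follow-up rule is explicit: no session, no contact. Exclusion from analysis is the natural reading of the other rule, since the only dropouts given intent-to-treat status are those with a completed session. The other reading is that never-starters stay in and all their post-test scores are imputed. The thresholds also differ in wording, attended in one place and completed in the other.

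**Shift in an arm mean.** Let p be the share of a randomised arm that never starts, and D the mean outcome of starters minus that of never-starters, in SD units. The article gives neither, so both are assumptions.

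- Mean of the full arm = (1 − p) × starters' mean + p × never-starters' mean.
- Starters' mean − full-arm mean = p × D.
- Bias in a comparison of arms A and B = p_A × D_A − p_B × D_B.

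The bias is zero with no never-starters, or when p × D is equal in the two arms. With never-starters in one arm only:

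| Never-starters of 25 | D = 0.25 | D = 0.5 | D = 1.0 |
|---|---|---|---|
| 1 (p = 0.04) | 0.01 | 0.02 | 0.04 |
| 3 (p = 0.12) | 0.03 | 0.06 | 0.12 |
| 5 (p = 0.20) | 0.05 | 0.10 | 0.20 |

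The article cites an effect range of 0.32 to 0.47. The middle cell is 0.06 / 0.47 = 13% to 0.06 / 0.32 = 19% of it. Against 0.32, the whole table runs from 0.01 / 0.32 = 3% to 0.20 / 0.32 = 62.5%.

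**Effect of baseline.** These are shifts in an unadjusted post-test mean. If the gap is D0 at baseline and D1 at 12 weeks, the shift in mean change is p × (D1 − D0). With D0 = D1 = 0.5 and p = 0.12 it is 0.12 × 0 = 0. With covariance adjustment and slope b on baseline it is p × (D1 − b × D0), which for these values and b between 0 and 1 lies between 0 and 0.06.

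**If never-starters are kept but mean-imputed.** The article does not say which mean is used. If it is the arm's observed mean, the arm mean stays at the starters' mean and the full p × D remains. The spread also shrinks: with 3 of 25 imputed in one arm and the other complete, the pooled variance is multiplied by (21 + 24) / (24 + 24) = 0.9375 and the SD by √0.9375 = 0.968, so d is inflated by 1 / 0.968, about 3%.

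**The case against.** The strongest reply is that this is a small pilot with no confirmatory test, and that the likely bias is minor beside its imprecision. For an unadjusted two-arm difference at 25 per arm the standard error is √(2/25) = 0.28 SD and the 95% half-width is about 0.55 SD, so a shift of 0.06 is roughly one fifth of a standard error. Entry requires willingness to be randomised, all three arms are supervised group exercise, and each takes 180 minutes a week (2 × 90 or 3 × 60). All of this stands and limits the likely size. It does not make the label right. Nor does imprecision excuse a selection that can be avoided, and non-starting by arm is itself a feasibility result, in a study that names feasibility as a purpose.

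Three stronger readings are tempting and not supported:

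- *The randomised comparison is broken.* It can be. Whether it is depends on the never-starters, and the article gives no count.
- *Yoga is the arm people want, so the controls will leave.* The article says nothing of the kind. The advertised features listed under Recruitment procedures do not mention yoga, and entry requires no yoga in the previous six months. The point needs only that the arms differ and are known.
- *The bias cannot be measured.* Baseline is complete before randomisation and attendance is recorded, so the number of never-starters and their baseline scores will be known by arm. Only their 12-week outcomes are missing.

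**Conclusion.** The point holds as a risk written into the plan. The one-session condition makes the set a modified one, non-starting can depend on a known allocation, and the Cohen's d values can be biased as a result. That never-starters leave the analysis is the natural reading, not an explicit statement; that they are not contacted is explicit. No size can be fixed from the article. Over the assumed range, with never-starters in one arm only, the unadjusted shift is 0 to 0.20 SD; the 0.06 SD case is an illustration. The shift is smaller for baseline-adjusted change to the extent that the gap already exists at baseline.

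**What to change.** - **Exercise logs, attendance, and adherence:** delete the one-session condition and invite every randomised participant to the 12-week assessment.
- **Statistical analysis:** analyse all randomised participants in the arm assigned, whatever their attendance. Do not fill never-starters' missing outcomes by mean imputation. Use a baseline-adjusted model or multiple imputation from baseline scores, with a sensitivity analysis for outcomes worse than baseline predicts.
- **Reporting:** give the number of never-starters and their baseline scores by arm.
- **One-session set:** keep it, if wanted, only as a sensitivity analysis labelled modified, and use one term for the threshold in both sections.

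The article gives a study period ending in May 2020 and was published in September 2020, so new follow-up may no longer be possible. In that case, relabel the set as modified and report never-starters by arm with the sensitivity analysis.

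The target of 75 does not change. The cost is, for a few more participants, two laboratory visits of roughly two hours, the questionnaires and a week of accelerometer wear. Some will decline, which is why the imputation method has to change as well.

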### Sample size calculation

We recognize that pilot studies do not typically report formal sample size calculations. However, to aid us in making advertising and recruitment decisions, we ran a very preliminary sample size analysis to get an estimated range of subjects needed. A meta-analysis of yoga effects on cognition [13] indicated an effect size range of .32–.47 (Hedge’s g) favoring the yoga condition. We based our sample size calculations to adequately power for a small effect within this range. Using an alpha of 0.05/2, a power of 0.80, and a conservative estimate of a medium effect size (*f* = 0.35), the desired total sample size is 75 (*N* = 25 per group) for this trial.

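### Mean imputation of missing week-12 scores biases the Cohen's d values that are the pilot's main output, in a direction that depends on an unstated choice of mean

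*Protocol article*

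**What the plan says.** All four statements come from Statistical analysis in the protocol article.

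- Missing data: "Missing data will be handled using a mean imputation approach". The sentence is not limited to questionnaire items or covariates, and it does not say which mean is meant.
- Analysis set, in the sentence directly before: "An intent-to-treat analysis approach will be used for any dropouts who completed at least one exercise session".
- Main output: "we will focus on descriptive statistics and calculating effect sizes (Cohen’s d values".
- Tests are optional: "Data characteristics permitting (normality, multi-collinearity, sample size), we may conduct additional secondary analyses". The example given is "a time (baseline, follow up) × group (yoga, aerobic, stretching-toning) repeated measures analyses of covariance controlling for relevant covariates".

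Elsewhere in the article, Measures sets one assessment before and one after the 12 weeks. Randomization requires complete baseline measurements before allocation. Exercise logs, attendance, and adherence says that dropouts who attended at least one session will be approached for follow-up testing. Strengths, limitations, and future considerations says that the results are hoped to inform a larger trial. No dropout rate is given.

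**The concern.** Because baseline is complete before allocation and there is only one follow-up, a missing cognitive outcome means a missing week-12 score. Dropouts are kept in the analysis, so that score is what the stated method would fill in. Placing identical values at the centre of a distribution lowers its SD, which is the denominator of Cohen's d. If the overall mean is used, the numerator also moves towards zero. Either way, d becomes partly a function of how many people were lost, and the dropout's observed baseline score, an obvious predictor of the missing value, goes unused.

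What is at stake is the planning value handed to the next trial. Required n is proportional to 1/d², so an error in d carries over squared.

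**Working it through.** **Inputs.** n = 25 per arm comes from Sample size calculation: "the desired total sample size is 75 (*N* = 25 per group) for this trial". That section cites a range of effects (g = 0.32 to 0.47); d = 0.40 is used below as a value inside it. Assumed because the article gives no figure: the share missing (8% to 40%), missingness completely at random and equal across arms, and, for the simulation, a baseline–follow-up correlation of 0.6.

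**The plan's own figure.** The total of 75 can be reproduced as a between-groups repeated-measures F test with 3 groups, 2 time points, f = 0.35, alpha 0.025, power 0.80 and an unstated correlation of 0.5. The noncentrality is f²·N·2/(1+ρ) = 0.1225 × 75 × 2/1.5 = 12.25. It does not depend on the imputation method and serves here only to set n.

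**Bias in d.** Let m of n scores be observed per arm.

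- Arm mean: the difference between arms is unchanged and the SD is multiplied by √((m−1)/(n−1)). With m = 20: √(19/24) = 0.890, so d is multiplied by 1/0.890 = 1.124 and 0.40 becomes 0.45.
- Overall mean: the SD shrinks by about the same factor and the difference is multiplied by m/n. With m = 20: 0.80/0.890 = 0.90, so 0.40 becomes 0.36.

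| Missing (m of 25) | SD factor | d factor, arm mean | d factor, overall mean |
|---|---|---|---|
| 8% (23) | 0.957 | 1.04 | 0.96 |
| 20% (20) | 0.890 | 1.12 | 0.90 |
| 28% (18) | 0.842 | 1.19 | 0.86 |
| 40% (15) | 0.764 | 1.31 | 0.79 |

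A simulation of 20,000 three-arm trials agrees. At 20% missing, a true 0.47 gives a mean d of 0.54 with the arm mean, 0.42 with the overall mean and 0.48 with observed cases only. The last value carries just the ordinary small-sample bias of d.

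**Consequence for planning.** At 20% missing, the arm mean would size the next trial at 1/1.124² = 0.79 of the n needed, and an intended 80% power falls to about 70%. The overall mean would oversize it by 1/0.90² = 1.23.

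**Optional tests, arm mean.** The naive standard error is 0.890 × √0.8 = 0.80 of the observed-case one. A large-sample check for two arms gives 1.96 × 0.80 = 1.57 and P(|Z| > 1.57) = 11.7%. Simulated type I error at nominal 5%:

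| Missing | Two-arm comparison, no baseline | Time × group on change | ANCOVA |
|---|---|---|---|
| 8% | 7.3% | 6.3% | 7.8% |
| 20% | 11.6% | 8.6% | 14.9% |
| 28% | 15.8% | 11.4% | 22.1% |
| 40% | 24.2% | 15.8% | 35.3% |

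**Optional tests, overall mean.** At 20% missing the true variance of the arm difference is 0.8² × 2σ²/20 = 0.064σ², and the naive variance is about 2 × 0.8σ²/25 = 0.064σ². They match, and simulated type I error stays between 4.7% and 5.4% throughout. The cost is power: for a true 0.47 at 20% missing, time × group power is 0.283, against 0.368 with observed cases.

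**The case against.** **The bias is small beside the noise.** With 25 per arm and d = 0.40, the standard error of d is about √(2/25 + 0.40²/100) = √0.0816 = 0.29. A shift of +0.05 or −0.04 is under a fifth of that. This stands and limits the severity. It does not justify the method, because the error is systematic and avoidable.

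**Little may be missing.** Dropouts who attended at least one session are to be contacted for follow-up testing, so leaving the exercise programme need not mean a missing score. At 8% missing, d is off by only about 3–4%. This stands too, and the size remains conditional on a rate that the article does not give.

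**Which mean is used may be stated elsewhere.** The article is condensed, and the choice among arm, overall and person or item mean could sit in a document not shown. That would settle the direction of the bias, but for a missing week-12 score neither the arm nor the overall mean avoids it.

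**Stronger readings that the text does not support.** A reader might infer that every test would have the wrong error rate. That is not so for overall-mean imputation with equal missingness. A reader might also treat the tests as part of the core output, but the article makes them optional. The figure of about 12% belongs to a two-arm comparison without baseline. The example model in the article is three-arm with time × group, for which the nearest figures are 8.6% and 14.9%.

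**Conclusion.** The point holds as a should-fix. As written, the method biases the pilot's main output: at an assumed 20% missing, d is about 12% too large with the arm mean or about 10% too small with the overall mean. At 8% missing the error is about 3–4%, and at 40% it reaches about 31% upward or 21% downward. No fixed direction can be asserted, so it would be wrong to read this as d always being inflated. Type I inflation is a secondary harm, confined to arm-mean imputation and to tests that may never be run.

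These figures rest on missingness completely at random and equal across arms, the case most favourable to mean imputation. They do not show that the pilot is invalid or that its sample size is wrong.

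**What to change.** Replace mean imputation of outcomes with one of the following, both available in the named software:

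- a likelihood-based mixed model of baseline and follow-up scores (SPSS MIXED); or
- multiple imputation by arm, using the baseline score and the stratification factors (sex, age, years since diagnosis).

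Compute Cohen's d with the baseline or observed-data SD, never an SD from filled-in data, and report the observed n per arm beside each d. If mean imputation was intended only for isolated questionnaire items, the text should say so.

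Who belongs in the analysis set is a separate question that this change does not touch.

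The cost is a few sentences of wording, slightly more analyst time, and less favourable precision than filled-in data would appear to give. No extra participants, visits or software are needed.
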